### Assumptions Underlying Sample Size Estimates:

### 7.1.3.a HIV Incidence of 4% Per Year

All estimates we have obtained are from settings that offer state-of-the-art HIV prevention services, such as HIV counseling and testing, condom distribution, and STI treatment, similar to what we offer in our trial. To ensure we can detect an effect, we have chosen a conservative strategy in estimating an HIV incidence of 4% in the non-diaphragm control arm, which is representative of the general population. Although realistically, incidence will vary somewhat by site (Table 4), 4% is a reasonable, overall estimate.

In South Africa for example, it is likely that the incidence is somewhat higher. This is based on an estimate of current HIV incidence data from Population Council ongoing Phase II trial in South Africa. An incidence of up to 5% in the first year of the trial may be more realistic here. However, this was a 12-month study and HIV incidence in our population may decline with a longer 24-months follow-up period.

In one of our cohort studies currently ongoing in Zimbabwe, we observed a yearly incidence rate of 3.74% among women who received quarterly a full package of HIV preventive services. In another condom promotion and counseling study, a yearly incidence of 4.8 % has been observed. Both are robust estimates observed after study of more than 3000 women over three years. Each estimate was derived from a target population identical to that proposed here. Thus, an average incidence rate of 4% seems realistic.

Together, estimates from the three sites indicate that an expected incidence rate of 4% is a reasonable overall average.

### 7.1.3.b Effectiveness of 33%

This Phase III study is powered to detect effectiveness (biological efficacy combined with adherence) of 33 percent. In Microbicide Efficacy Trial Design Meetings convened in January 1998 and August 2000, comprehensive groups of scientists considered key methodological issues and agreed at both meetings that an effect size of 33 percent was justifiable. This effect size also is consistent with the current recommendations of the International Working Group on Microbicides. The HIV Prevention Trials Network (HPTN) also uses 33% as their effect size. Additionally, this is consistent with the figure employed in most HIV vaccine trials. Reduction in risk of one-third would have an enormous impact on the epidemic. Although it necessitates a larger sample size, a trial capable of detecting a smaller effect size lowers the chances that a life-saving technology will be discarded for failing to clear an unreasonably high hurdle.

### 7.1.3.c Two-tailed versus One-tailed

Despite the fact that the diaphragm is unlike some candidate microbicides whose mechanism of action is to break down cell walls of both HIV and the cervical epithelium, the possibility remains that diaphragm use may be associated with increased infection risk via unknown mechanisms. For this reason, we felt that a two-tailed test would be most appropriate.

### 7.1.3.d Confidence of 95% (α=0.05) and Power of 90%

If HIV incidence is higher than we estimated, we may achieve higher than expected statistical power, or may be able to stop the study early. A DSMB will review interim data after one-third of expected HIV seroconversions—approximately 100 events—have occurred.

Each study site has established participant retention procedures to achieve loss-to-follow-up rates that do not exceed the HIV infection rate among local study participants to minimize potential bias associated with loss-to-follow-up. However, the assumed overall retention rate of 80% was factored into the sample size calculations to adjust for the increase in variability associated with these rates.

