# 2 Study Summary

**Study Purpose:** To determine the effectiveness of the diaphragm with Replens lubricant gel in the reduction or prevention of the heterosexual acquisition of HIV among women.

**Study Design:** Multi-site randomized, controlled, trial with two study arms:

1) Ortho All-Flex Arcing Spring latex diaphragm with Replens lubricant gel, and 2) a non-diaphragm and gel control arm.

Women in both arms receive male condoms, safer-sex counseling, and diagnosis and treatment of sexually transmitted infections.

**Sample Size:** 5,000 women (2,500 per arm) seen for an average of 18 months (range of 12-24 months of follow-up).

**Study Population:** HIV-negative, sexually active, non-pregnant women.

**Visit Schedule:** Screening, enrollment, two-week post-enrollment visit, and 4 to 8 quarterly visits depending on date of enrollment. Optional visits any time for counseling, obtaining additional supplies, or other concerns.

**Study Duration:** Approximately 48 months total, with 6 months for start up activities and 6 months for analysis and write-up.

**Primary Objectives:** To determine the effectiveness of the diaphragm with Replens

lubricant gel in preventing heterosexual transmission of HIV

among at-risk women.

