# 4 Study Objectives and Design

We are conducting a prospective, randomized, controlled, effectiveness trial of the diaphragm with lubricant gel at three sites, one in Zimbabwe and two in South Africa. We offer all women in the trial an HIV prevention package that includes HIV testing, safer sex counseling, free male condoms, and diagnosis and treatment of STIs. At each site, women are randomized into two groups. One of these groups receives latex diaphragms with Replens lubricant gel and counseling and training on how to use them while the other does not. We are following women quarterly for up to two years. We are measuring the incidence of HIV, cervical STIs (*Chlamydia trachomatis*, *Neisseria gonorrhoeae*), and other STIs (*Treponema pallidum*, *Trichomonas vaginalis*, and HSV-2), and will compare rates between the two groups. Because our main intervention of diaphragm with lubricant gel is offered as part of an HIV prevention package, we expect that HIV rates in both the intervention and control arms likely will be lower than those observed in the community at large. We took this into account in our sample size calculation.

We are enrolling 5,000 women who will be seen over a 12 to 24 month period, totaling approximately 7,000 woman-years of follow-up. This estimate was based on the expectations that there would be an average HIV incidence rate of 4%, that each woman we enrolled would participate on average 18 months, and that discontinuation rates would be 6-7% per year for a total of approximately 20% over the study period (3 years of field work). The expected discontinuation rates were based on on-going cohort studies at two of the sites and include true loss-to-follow-up (*i.e.* women who are lost and who have no outcome data). See section 7 below for sample size details and justification.

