# 7 Accrual, Follow-up, and Sample Size

## 7.1 Primary Endpoint

**7.1.1 Required sample size**

Sample size calculations are made by comparing HIV incidence rates between study arms using a log rank test stratified by study site and using approximate methods described by Lachin and Foulkes. 26We initially assumed that participants will be recruited over a period of 2 years, that the duration of the study would be 3 years, and that annual HIV incidence in the non-diaphragm arm (control group) would be approximately 4%, 5% and 3.5%at the Harare, Durban, and Johannesburg sites respectively. We further assumed that these sites would contribute 49%, 29%, and 22% of the total sample respectively and that discontinuation rates, including lost to follow up and true discontinuations, would not exceed approximately 7% per year at all sites or a total of approximately 20% over the three-years field implementation period. With these assumptions we required a total of 4500 women to have 90% power to detect a 33% treatment-related reduction in incidence as significant at the 5% level, assuming a two-sided alternative. This sample size and the assumption of constant rates of recruitment and censoring implies that approximately 4000 woman years of follow-up will be required per arm to detect a treatment-related reduction in incidence of 33%. This corresponds to a total of approximately 293 total serconversions in both arms combined. The following table presents enrollment goals and expected numbers of seroconversions by site.

**Table 4***: Approximate numbers of women to be enrolled to reach required number (293) seroconversions. We assume approximately 20% discontinuation rate at each site over the entire study period.*

|  | **Enrolled** | **Estimated annual incidence (overall)** | **Minimum estimated**  **Infections** |
| --- | --- | --- | --- |
| Harare | 2200 | 4% | 134 |
| Durban | 1300 | 5.0% | 99 |
| Johannesburg | 1000 | 3.5% | 60 |
| **Total** | **4500** | **~4.0%** | **293** |

If incidence is actually higher than assumed here, the diaphragm actually confers more than 33% protection, or the discontinuation rate is lower, it may be possible to end the study early. This decision will be made via stopping rules that will be considered during the interim analysis conducted by our DSMB (section 12.6. below).

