- Update locator information. Exiting participants will be asked for updated contact information and to sign a form indicating their permission or not to contact them after their participation in the trial is completed in order to inform them about trial results, inquire about study product use experience, and/or to participate in future trials.

Women only receive a pelvic exam when clinically indicated. Instructions for complete documentation of AEs and SAEs appear in Section 11. If a women tests positive for HIV or STIs, or if any other abnormalities are found, we provide treatment as outlined in Sections 9.8 and 9.10.

Women may participate and be followed in the study for up to 24 months.

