## Cohort Retention

Once a participant enrolls in this study, the study site makes every effort to retain her in follow-up to minimize possible bias associated with loss-to-follow-up. Each site has established participant retention procedures to strive for loss-to-follow-up rates that do not exceed the incidence rate of the primary study endpoint. As such, an average annual retention rate of 93% including drop-out and true loss-to-follow-up is targeted across sites. Study site staff are responsible for developing and implementing local procedures to achieve this goal. Components of such procedures include:

- Thorough explanation of the study visit schedule and procedural requirements during the informed consent process, and re-emphasis at each study visit.
- Thorough explanation of the importance of both study treatment groups to the overall success of the study.
- Collection of detailed locator information at the study Screening Visit and active review and updating of this information at each subsequent visit; locator information may be verified for follow-up purposes.
- Use of mapping techniques to establish the location of participant residences and other locator venues.
- Use of appropriate and timely visit reminder mechanisms.
- Immediate and multifaceted follow-up on missed visits. If a participant is more than one week late for a scheduled visit, attempts are made to locate the participant. If a participant returns to the clinic for a quarterly follow-up visit more than 5.5 months after the scheduled visit date, the visit is considered a missed visit and the next quarterly visit is completed instead.
- The use of trained outreach workers to trace participants and visit them regularly at their homes and/or other community locations when compatible with confidentiality requirements. This is standard procedure even in Zimbabwe where we usually see participants in the clinic. Missed visits are followed by tracing in the community and a possible home visit.
- Regular communication with the study community at large to increase awareness of HIV/AIDS and explain the purpose of HIV prevention research and the importance of completing research study visits.

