**Statistical power.** For study aims #1-3, we calculated minimal detectable relative hazards for the main study outcomes based on the sample size of 2,200 enrollees with a 10% loss-to-follow-up rate, a power of 80% and a significance level of 5% (one-tailed alpha=0.05) using the log-rank test. We chose one-sided tests for this analysis since we do not believe that diaphragms increase risk of HPV outcomes. We performed analyses over a range of plausible prevalence rates of HPV (up to 40% for all types and as low as 20% for high-risk types) and evaluation periods (12 to 24 months). Prior studies of Zimbabwean sero-negative women have indicated a prevalence of HR HPV types of 28% 64. We assumed an annual HR HPV incidence rate of 8% and an annual clearance of 65% in the non-diaphragm arm based on studies from a high-risk area of Brazil 65. The prevalence of cytologic abnormalities was estimated at 15% and incidence at 10% per year in this high-risk population in the non-diaphragm arm. High-grade cervical intraepithelial neoplasia (CIN 2 or worse) prevalence was estimated at 5.9% based on a prior cross-sectional study in Zimbabwe 64. Assuming a cytology sensitivity of 62% 64 and an annual incidence rate of 0.5%, we estimated a prevalence of CIN 2 or worse of 3% by the end of the study in the non-diaphragm arm. For study aim #4, we assumed that 88 women would sero-convert to HIV-positive over the course of the study. We determined the minimal detectable odds ratios for a range of prevalence rates of predictors (e.g., HPV) at 80% power and one-tailed alpha of 0.05.

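### The 20% discontinuation / 80% retention figure compounds 7% a year over three calendar years, but each woman is followed 12 to 24 months, so it does not match the 7% annual assumption or the 93% annual target

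*Protocol*

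**What the plan says.** **Assumed loss.** Section 4 expects that "discontinuation rates would be 6-7% per year for a total of approximately 20% over the study period (3 years of field work". Section 7.1.1 says that discontinuation "would not exceed approximately 7% per year at all sites or a total of approximately 20% over the three-years field implementation period", and the Table 4 caption adds: "We assume approximately 20% discontinuation rate at each site over the entire study period". Section 7.1.3.d carries this forward as the statement that "the assumed overall retention rate of 80% was factored into the sample size calculations".

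**Follow-up per woman.** Section 2 has women "seen for an average of 18 months (range of 12-24 months of follow-up" as the stated range. Section 9.5 says: "Women may participate and be followed in the study for up to 24 months".

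**Operational target.** Section 9.9 states that "an average annual retention rate of 93% including drop-out and true loss-to-follow-up is targeted across sites". Sections 7.1.3.d and 9.9 also ask sites to keep loss no higher than HIV incidence.

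**Use of the assumption.** Under Section 12.6 the inputs to the sample size, including retention at each site, are assessed at the interim review, and the sample size may be altered on the DSMB's recommendation.

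**The concern.** Loss to follow-up accrues over the time each woman is at risk of leaving, not over the calendar length of the field work. Staggered entry makes the field period three years, but a woman contributes at most two. A three-year cumulative loss therefore describes nobody in the trial, and its complement is not an overall retention rate.

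What is at stake is the reference used at the interim review. Section 7.1.1 gives 7% a year and 20% in total as alternative statements of one assumption, and the Table 4 caption applies the 20% to each site. Over 12 to 24 months they are different assumptions, about a factor of two apart on average. Someone checking a site against the sample-size inputs would reach different conclusions depending on which figure was used. The same three-year clock also appears in the woman-year requirement of 7.1.1, which affects how the 293 events are to be reached.

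**Working it through.** **Inputs.** Annual loss d = 7% (Section 7.1.1; 6 to 7% in Section 4). Follow-up 12 to 24 months, mean 18 (Sections 2 and 4). Accrual 2 years and study duration 3 years in the sample-size model (Section 7.1.1). N = 4,500, later 5,000. Woman-years: 4,000 per arm (Section 7.1.1) and about 7,000 in total (Section 4). The documents do not give the distribution of follow-up, so uniform follow-up is assumed where an average is needed.

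**1. Reproduce the stated figure.** Cumulative loss = 1 − (1 − d)^t. With t = 3: 1 − 0.93³ = 1 − 0.804 = 19.6%. This is the stated 20%, and its complement is the 80%.

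**2. Same formula on the actual follow-up.**

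| Time on study | Retained | Lost |
|---|---|---|
| 12 months | 0.93 = 93.0% | 7.0% |
| 18 months | 0.93^1.5 = 89.7% | 10.3% |
| 24 months | 0.93² = 86.5% | 13.5% |

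**3. Average over women.** With hazard η = −ln 0.93 = 0.0726 and follow-up uniform on 1 to 2 years, mean retention = (0.93 − 0.8649)/0.0726 = 0.897, a loss of 10.3% (8.8% at 6% a year).

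**4. Sensitivity to the follow-up pattern.**
- Two-year accrual in a three-year study, each woman stopped at 24 months (mean 21 months): 11.9%.
- The uncapped 1-to-3-year model implied by 7.1.1: 1 − (0.93 − 0.8044)/(2 × 0.0726) = 13.4%.

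No follow-up pattern described in the protocol gives an average of 20% at 7% a year.

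**5. What 20% would require.** Over 18 months, 1 − 0.80^(1/1.5) = 13.8% a year. The ratio of 20% to 10.3% is 1.9; for a woman followed the full 24 months it is 20/13.5 = 1.5.

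**6. Woman-years: which clock was used where.**
- Section 4: 7,000/5,000 = 1.40 years per woman. Uniform 1 to 2 years at 7% loss gives 0.1029/0.0726 = 1.419 years, or 7,093 woman-years for 5,000 women. It is 6,907 if time also stops at seroconversion, using the site incidences of 7.1.1 for controls and a hazard ratio of 0.67. Both agree with about 7,000.
- Section 7.1.1: 2 × 4,000 = 8,000 woman-years. This is 1.78 years per woman at N = 4,500 and 1.60 at N = 5,000. Both exceed the 1.5-year average follow-up even with no loss at all. The figure is reproduced only with follow-up of 1 to 3 years: 4,017 per arm at N = 4,500 and 7% a year, on the same model. With 12 to 24 months that model gives 3,109 per arm at 4,500 and 3,453 at 5,000.

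Both woman-year figures fit an annual rate of 7%; they differ in the follow-up clock.

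**The case against.** Three arguments carry weight.

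First, a reader might infer that the protocol would accept twice the planned loss, since a site losing almost 14% a year would end near 80% retention. The documents do not support that reading. The 80% is described only as a sample-size input. Section 9.9 sets 93% a year as the target and Section 9 provides for action when retention falls below it; loss is also to stay within HIV incidence. Section 7.1.1 itself caps discontinuation at about 7% a year, so a site at 14% breaches the stated assumption. This objection stands in full.

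Second, the 20% is labelled as covering three years, and for three years it is correct. The label is present in Sections 4 and 7.1.1 but is lost in 7.1.3.d, where 80% becomes an overall retention rate. A correct three-year sum still does not apply to women followed for at most two.

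Third, the woman-year figures suggest that 7% a year, rather than a flat 20%, drove the calculations, and an overstated loss only enlarges the sample. Both are fair. They limit the consequence but leave the text inconsistent.

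The appendices do not settle the matter. The HPV sub-study's power rests on a "sample size of 2,200 enrollees with a 10% loss-to-follow-up rate", which is close to the average found here, but it is a single-site assumption. The bacterial vaginosis sub-study uses 5% a year, and the male-partner study's 10% sizes a sample largely at month 12.

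**Conclusion.** The inconsistency is real. At the protocol's own 7% a year, expected loss is 7.0% at 12 months, about 10% on average and 13.5% at 24 months, against a stated 20%. The average rests on a constant annual rate and roughly uniform follow-up over 12 to 24 months; other readings of the accrual pattern move it to between about 9% and 13%, never to 20%.

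The consequence is moderate. Taken alone, the overstatement is conservative for sample size, and nothing in the protocol plans for or tolerates 20% loss. Figures such as 1,000 of 5,000 women lost would arise only if sites actually lost about 14% a year, so they are not a cost of the plan as written. The defect is that two non-equivalent retention assumptions are offered for the sample-size review in Section 12.6, and that the same three-year clock leaves 8,000 woman-years in 7.1.1 beside about 7,000 in Section 4. It should be corrected.

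**What to change.** 1. In Section 4, Section 7.1.1 (text and Table 4 caption) and Section 7.1.3.d, replace the 20% and 80% figures with the annual rate and per-woman cumulative retention: 93% at 12 months, about 90% on average, 86.5% at 24 months. Cross-refer to the 93% annual target in Section 9.9.
2. In Section 12.6, name 7% a year as the retention assumption assessed at each site.
3. Re-state the woman-year and event figures of 7.1.1 on the 12-to-24-month time base, so that they agree with Section 4.

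**Cost.** Items 1 and 2 are wording only. Item 3 needs a recalculation and should not be skipped: putting about 10% into 7.1.1 while leaving its three-year model in place would create a new mismatch, because that model averages 13.4%. The re-stated numbers will also be lower. With the stated site incidences taken as control rates, a hazard ratio of 0.67, 7% annual loss and uniform 12 to 24 months, expected events are about 217 at 4,500 women and about 242 at 5,000, against the 293 stated. The sponsor would then need to say how the 293 are to be reached, or what power the smaller number gives.

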## Secondary Endpoints

Although the primary endpoint of this trial is HIV infection, we are studying other sexually transmitted pathogens as secondary endpoints. Evidence from a recently completed Phase II Population Council microbicide trial in South Africa suggests that the incidence of *Chlamydia trachomatis* will be higher than the incidence of HIV and the incidence of *Neisseria gonorrhoeae* will be similar to the incidence of HIV. In our current studies in Zimbabwe, incidence rates for *Chlamydia trachomatis* and *Neisseria gonorrhoeae* mirror those we observed for HIV and is higher for *Trichomonas vaginalis*. A very high incidence rate for HSV-2 is expected as well. Thus, our sample size will be adequate to also assess the effect of the latex diaphragm used with lubricant gel against these pathogens. Additionally, we will evaluate them as potential effect modifiers of a diaphragm-HIV relationship.

# 8 Study Products

## Composition of Study Products

**Diaphragm**

The All-Flex Arcing Spring diaphragm (Ortho-McNeil Pharmaceutical, Inc.) is a molded, buff-colored, natural rubber vaginal diaphragm containing a distortion-free, dual spring-within-a-spring that provides unique arcing action.

**Lubricant Gel**

Replens (Lil’ Drug Store Products, Inc.) is an over-the-counter vaginal moisturizer which has been used as a placebo in recent microbicide safety and effectiveness trials.27,28,29 Ingredients include purified water, glycerin, mineral oil, polycarbophil, carbomer 934P, hydrogenated palm oil glyceride, sorbic acid, methylparaben, and sodium hydroxide. Replens is not a known contraceptive.

